#### Design

This study will comprise of three experiments, by which we aim to decompose the parental involvement in a more detailed manner, to test if it moderates susceptibility to outcome bias in parents. Specifically, we will test if parents differ in biased reasoning from non-parents (experiment 1), do those two groups differ when judging about involving decisions (experiment 2), and finally do parents show higher understanding for other parents' decisions, in comparison with non-parents as judges (experiment 3). The design of all three experiments is mixed, 2 × 2 with two groups of participants, parents and non-parents.

Experiment 1 (Parenting and biased reasoning): 2 (levels of domain: health and non-health) × 2 (outcomes).

Experiment 2 (Parenting and involvement): 2 (levels of involvement) × 2 (outcomes)

Experiment 3 (Parenting and solidarity): 2 (levels of protagonists: parents and non-parents) × 2 (outcomes).

The independent variables, the domain, level of involvement in the decision, and protagonist will have two levels: health (e.g., Vitamin supplementation) and non-health domain (e.g., free time); low (e.g., should protagonist give a vitamin supplement to a child or not), and high involvement (e.g., should protagonist vaccinate a child or not); and who is making a decision (parent as protagonist or non-parent as protagonist). The outcome variable will have two levels: the positive and the negative outcome. By crossing two levels of each binary independent variable in all three experiments (domain, involvement, decision maker) with the parenthood of participants (parents and non-parents), four experimental situations will be formed: parents in, e.g., high involvement situation, parents in low involvement situation, non-parents in high involvement situation, non-parents in low involvement situation (see Table 2). Every situation will be formed with both outcomes (see Table 3). Equivalent design will be applied in all three experiments.

**Table 2 T2:** Experimental situations in all three experiments.

	**Experiment 1 (domain)**		**Experiment 2 (involvement)**		**Experiment 3 (protagonist)**	
Factor levels	H	nH	hI	lI	P	nP
Parents	P × H	P × nH	P × hI	P × lI	P × x P	P × nP
Non-parents	nP × H	nP × nH	nP × hI	nP × lI	nP × P	nP × nP

*H, health-related; nH, non health-related; hI, high involvement; lI, low involvement; P, parent; nP, non parent*.

**Table 3 T3:** Tasks for all three experiments.

	**Domain**		**Involvement**		**Protagonist**	

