Factor levels	H	nH	hI	lI	P	nP
Positive outcome (+)	H+	nH+	hI+	lI+	P+	np+
Negative outcome (−)	H−	nH−	hI−	lI−	P−	nP−

*H, health-related; nH, non health-related; hI, high involvement; lI, low involvement; P, parent; nP, non parent*.

Each subject will participate in the procedure in two time slots, separated by 1 week (with opposite outcomes). For each experimental situation, a Latin square design will be used for randomizing the order of presentation of experimental tasks during two experimental sessions.

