### Proposed analysis

The aim of this study is to investigate the moderating role of involvement in susceptibility to outcome bias.

Like in study 1, different samples will be treated separately. We will be using R and Matlab to conduct our analysis.

There is a possibility that participants might remember their answer from the first session and adapt their answer in the second session accordingly. To control this, we will use a two-way ANOVA. We will test whether the order of presentation of the stimuli, particularly whether the positive or negative outcome presented first, has an influence on the answers obtained during the second session.

To test our hypotheses, we will use a bivariate analysis of variance with repeated measures. As measures of the outcome bias, the difference between mean evaluations of decisions with positive and negative outcomes will be used to form 2 new variables for each of the 3 experiments. These new variables will then be used in the analysis. We will verify the assumption of standard distribution by conducting a Kolmogorov-Smirnov Test. If we cannot assume standard distribution, we will use the Wilcoxon signed rank test instead of an ANOVA. Effect sizes for each pair of tasks will be presented as Cohen's D.

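### Study 2 checks presentation order in a stand-alone ANOVA; carrying the randomised order into the difference-score model would protect precision at almost no cost

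*Protocol article*

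**What the plan says.** All of this is in the protocol article, Study 2.

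- **Groups (Design).** "The design of all three experiments is mixed, 2 × 2 with two groups of participants, parents and non-parents". The second factor is domain, involvement or protagonist, according to the experiment.
- **Sessions (Design).** "Each subject will participate in the procedure in two time slots, separated by 1 week (with opposite outcomes").
- **Order (Design).** "For each experimental situation, a Latin square design will be used for randomizing the order of presentation of experimental tasks during two experimental sessions".
- **Order check (Proposed analysis).** The section recognises that participants may recall their first answer and adjust the second. It continues: "To control this, we will use a two-way ANOVA". The test is "whether the positive or negative outcome presented first, has an influence on the answers obtained during the second session".
- **Hypothesis test (Proposed analysis).** "To test our hypotheses, we will use a bivariate analysis of variance with repeated measures". Its variables are positive-minus-negative difference scores, two per experiment, one for each factor level: "the difference between mean evaluations of decisions with positive and negative outcomes will be used to form 2 new variables for each of the 3".

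The article does not say what follows if the order check is positive, and it names no order or session term for the hypothesis model.

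**The concern.** Outcomes are reversed between sessions, so the two ratings that form a matched pair come from different sessions. If ratings drift between visits, the drift enters the difference score with a sign that depends on which outcome came first. Randomising the order keeps the drift out of the group means on average. It does not take the drift out of the residual unless order is in the model.

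A separate test of second-session answers removes no variance from the hypothesis test, so it does not deliver the control that the section attributes to it. The tests exposed are the parent versus non-parent comparisons, which carry the Study 2 hypotheses and for which the article states no power.

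**Working it through.** **1. The plan's own figure.** The Sample section gives 99.9% power for detecting outcome bias (effect size 0.7, p < 0.01, 20 per experimental group). The metric of the 0.7 is not stated. Read as f with 1 df and 4 × 20 = 80 subjects, power is 0.9998; read as a paired standardised difference with n = 80, it is also 0.9998. Both agree with the stated figure. It concerns outcome bias itself, not the parent/non-parent contrast.

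**2. Effect of a session shift.** Let sigma be the SD of the difference score without a shift, and delta the additive shift from session 1 to session 2. If all positive outcomes at a level fall in one session:

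- positive first: D = bias − delta
- negative first: D = bias + delta

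With order split equally within each group, delta cancels from the group means, but Var(D) = sigma² + delta². In units of sigma, the variance rises by 1% at delta 0.1, 6% at 0.25, 25% at 0.5 and 100% at 1.0.

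**3. Scale of sigma.** From the third pilot study, taking 48 error df: (6.02 − 3.56) × √49 / √283.239 = 1.02 points on a 10-point scale. This is only a rough guide. Study 2 rates from −3 to +3, and the pilot also used two sessions, so its SD may already contain a shift.

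**4. Illustration for one difference score.** The document gives no delta, so a range is assumed. The contrast is parents versus non-parents, order exactly balanced, two-sided alpha 0.01. The 0.7 SD and 20 per group are borrowed from the outcome-bias power statement; 222 per group is the Study 1 minimum per country, assuming all Serbian parents continue and are matched one to one.

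| n per group | effect (SD) | delta (SD) | power without order | power with order |
|---|---|---|---|---|
| 20 | 0.7 | 0 | 32% | 32% |
| 20 | 0.7 | 0.1 | 32% | 32% |
| 20 | 0.7 | 0.25 | 30% | 32% |
| 20 | 0.7 | 0.5 | 22% | 32% |
| 20 | 0.7 | 1.0 | 6% | 32% |
| 222 | 0.3 | 0.5 | 61% | 72% |
| 222 | 0.5 | 0.5 | 99.1% | 99.6% |
| 222 | 0.7 | 1.0 | about 100% | about 100% |

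With no true difference and 20 per group, the test without order rejects less often than its nominal 5%: about 2.9% at delta 0.5 and 0.6% at delta 1.0. It is conservative.

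**5. Which test is affected.** Simulation with two difference scores per participant (correlation 0.5 assumed), 20 per group, effects of 0.7 SD, alpha 0.01, delta 0.5 SD:

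| Layout | Parenthood main effect, without / with order | Parenthood-by-level interaction, without / with order |
|---|---|---|
| Same outcome order at both levels | 21% / 33% | 33% / 33% |
| Opposite order at the two levels | 33% / 33% | 6% / 32% |
| Outcomes balanced within session at each level | no loss | no loss |

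The article does not say which layout the Latin square produces.

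**The case against.** **Order is not ignored, and an article condenses.** The same section names the risk and plans a test for it, and full model terms may sit in an analysis plan that is not shown. Silence about an order term is therefore weak evidence of exclusion. What remains is that the article does assign order a place, in a separate test of second-session answers, and presents that as control. A better placement is available.

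**Not every shift costs power.** A reader might infer that any session shift inflates the error term. The documents do not support that. Scores are means over tasks, and if positive and negative tasks are balanced within session at each level, the shift cancels within each participant. Otherwise the loss falls on the main effect or on the interaction, depending on layout. The Study 2 Introduction predicts interaction-type patterns for experiments 1 and 3, and these are untouched if order is the same at both levels.

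**The figures are borrowed.** Delta is assumed, and the 0.7 and 20 per group come from a statement about outcome bias. The low baseline of 32% comes from that transfer. With 222 per group and an effect of 0.5 SD or more, the loss at delta 0.5 is under one percentage point. All of this stands.

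**Bias and the stated power.** A reader might also infer a biased contrast or a threat to the 99.9%. With balanced order the estimate is unbiased. Bias would need order to become unequal between parents and non-parents, for instance through missed second visits, and the documents give no figure suggesting this. Nor is the 99.9% shown to be at risk: the pilot, also run in two sessions, gave a bias of about 2.46 / 1.02 = 2.4 SD of the difference.

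**Conclusion.** The point holds as a precision issue to consider. The order check stands apart from the hypothesis model and cannot remove session variance from it. Where a participant's positive and negative outcomes at a level fall in different sessions, a shift delta adds about delta² to the variance of the difference score and makes one parent/non-parent test conservative.

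The size is unknown, because neither delta nor the layout is given. On the illustrative figures the loss is about 2 points of power at delta 0.25 SD and 10 points at 0.5 SD with 20 per group, about 11 points with 222 per group and a 0.3 SD effect at delta 0.5, and negligible for small shifts or larger effects at that sample size. The analysis is not invalid.

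**What to change.** In Study 2, Proposed analysis, add the randomised order (positive-first or negative-first) as a between-participant factor, with its interaction with level, to each difference-score ANOVA. The interaction is needed because under opposite order at the two levels the shift appears there.

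Alternatively, fit an equivalent mixed model to the ratings with outcome, level, parenthood and their interactions, session, and participant random effects. These should let outcome bias vary between participants, so that the error term matches that of the difference-score analysis.

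State that conclusions come from this model whatever the preliminary order test shows.

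The cost is a sentence of text and one or two residual degrees of freedom. In the calculations above the added term cost no measurable power when delta was zero. No new data are needed, since order is assigned by design.

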## Joint discussion

With both studies we aim to investigate and come closer to understanding factors which influence vaccine hesitancy as a possible outcome of the vaccine-related decision-making processes, while focusing on testing the role of the involvement, as a potential underlying factor which skews this decision. Results of Study 1 will provide further insights into factors serving as reinforcements of the delay and omission of vaccination but also factors serving as reinforcements of the intention to vaccinate, as well as their interrelatedness. The results will provide insights into the construct of vaccine hesitancy that is currently lacking different stakeholders combating dropping immunization rates.

Moreover, if the Study 2 yields results consistent with our hypotheses, we will gain valuable proof that in terms of the extent and lengths of the decision-making processes regarding vaccination of their children, parents are indeed a special group, different from people without children, who do not have to face such dilemmas, and are therefore susceptible to different cognitive obstacles to reaching a decision to vaccinate.

With such knowledge it would be possible to draft interventions custom-made for parents aimed toward undermining their vaccine hesitancy by establishing better communication channels and better, more effective formation of relevant, informative and non-patronizing messages, addressing their personal dilemmas and fears with respect and understanding. Parents might not be afraid of vaccine-preventable diseases, but it seems they are afraid of vaccines – and the burden of the immunity of our herd lies on their shoulders.

## Ethics statement

This study was carried out in accordance with the recommendations of the Institutional Review Board of the Faculty of Philosophy of the University of Belgrade, who also ethically approved the proposed studies. All subjects gave written informed consent in accordance with the Declaration of Helsinki. The protocol was approved by the Institutional Review Board of the Faculty of Philosophy of the University of Belgrade.
